### Non-Study Treatments

Responsibility for the management of participating patients rests with their own clinicians, who are free to initiate, alter, or cease any treatment as clinically appropriate. Specifically, management of hypertension, volume status, acidosis, potassium, anemia, bone mineral metabolism, cardiovascular risk reduction, infection, dialysis modality planning and initiation, kidney transplant referral, and advanced care planning will be left to the discretion of the patients’ clinical care team.

### Follow-up Visits

Patient-Reported Outcome Measures (using KDQOL-SF) and Experience Measures (PREM) will be measured at baseline, 3, 6, 9, and 12 months (or at baseline and subsequently every 3 months until the initiation of the dialysis). The validated tools used will be the UK Kidney PREM (adapted to CKD), which measures several patient experience domains relevant to CKD, and the KDQOL-SF, which measures health-related quality of life. Each of these surveys takes about 15 to 20 minutes to complete.

Usability, acceptability, and patient perspective on the intervention will be assessed at the end of the trial (12 months or at the time of dialysis initiation) using the System Usability Scale (SUS) survey, which will be sent via REDCap link.

Finally, the occurrence of primary and secondary outcomes (defined below) will be assessed at all follow-up visits.

### Exit Focus Groups/Interviews

Participants in the intervention group will be asked to participate in a virtual exit focus group/interview at the end of the study (ie, at 12-month follow-up or upon dialysis initiation). Informed consent will be obtained to record and transcribe the focus groups/interviews for thematic analysis. The purpose of these focus groups/interviews will be to describe the subjective patient experiences of using VIEWER. The focus groups/interviews will be semi-structured, and interviewers will be provided a list of topic areas germane to the patient experience that should be discussed during the focus group/interview.

## Outcomes

### Primary Outcome

Our composite primary outcome will be time to first hospitalization or first ED visit.

### Secondary Outcomes

Individual components of the composite outcome.All-cause mortality.Acute inpatient initiation of dialysis.UK Kidney PREM score (adapted to CKD).Kidney Disease Quality of Life-Short Form (KDQOL-SF) score.System Usability Scale (SUS).Frequency of formal clinic visits.Adherence.Qualitative outcomes: provider and patient perspectives (qualitative).

## Statistical Methods

### Primary Analysis

Our primary analysis will take an intention-to-treat (ITT) approach. The primary outcome (time to first hospitalization or ED visit, censoring at dialysis or death) will be compared between groups using a Kaplan-Meier analysis with a log-rank test.

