## Abstract

**Background::**

The transition from advanced Chronic Kidney Disease (CKD) to dialysis is a period of heightened vulnerability for many patients. Virtual monitoring of these patients could facilitate the communication of accurate and reliable data between patients and health care providers, helping to avoid unnecessary emergency department (ED) visits and facilitate more optimal dialysis starts.

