**Methods::**

Intention-to-treat (ITT) approach will be used to compare the primary outcome between 2 study groups. Time to primary and secondary outcomes will be assessed using univariate Cox proportional hazards models and a Kaplan-Meier analysis with a log-rank test. The primary outcome is the time to first hospital admission and/or ED visit. The control is usual care (no exposure to VIEWER platform).

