### Sample Size Considerations

Based on systematic reviews of the published literature, we estimate a 39% reduction in the hazard of an outcome event (ie, hazard ratio [HR] = 0.61 for intervention).^6,7^ Further assuming an event rate in the usual care group of 11.4% per month,^
7
^ an expected median follow-up of 12 months per patient, a censoring rate of 3% per month, patient attrition of 10%, 2-ided alpha = 0.05, and beta = 0.10 (90% power), we will require 340 patients total (170 per arm), 68 patients/site.

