**Figure 1. fig1-20543581251359736:**
[figure not shown]
Study flow: 340 eligible participants will be randomly assigned to either the intervention group (receiving usual care along with the VIEWER virtual care platform) or the control group (receiving only usual care). Participants will be followed for 1 year or until dialysis initiation. Participants in the intervention group will receive a wireless BP cuff, weight scale, transcutaneous O_2_ saturation (SpO_2_) monitor, wearable motion tracker, and a mobile tablet with the VIEWER application. They will be trained to use the VIEWER platform while continuing to receive usual care. Participants in the control group will receive usual care without additional devices or platforms. All participants will complete the UK Kidney PREM score (adapted for CKD) and the Health-related Quality of Life using KDQOL-SF via REDCap or paper forms at baseline, 3, 6, 9, and 12 months (or every 3 months thereafter until dialysis initiation). At the end of the study, virtual interviews or focus groups will be conducted with a subset of participants from the intervention group and health care providers.

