### Economic Assessment

We will use event rates and direct costs derived from the trial to re-calibrate our previously published Markov cost-effectiveness model in determining the cost utility of this intervention.^
14
^

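### Kaplan-Meier curves that censor dialysis and death will overstate the 12-month risk of an ED visit or admission; the log-rank test stays valid, but only for the pre-dialysis, cause-specific hazard

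*Protocol article*

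**What the plan says.** The Primary Analysis section defines the outcome as "time to first hospitalization or ED visit, censoring at dialysis or death" and says that it "will be compared between groups using a Kaplan-Meier analysis with a log-rank test". The abstract's Methods paragraph adds a model: "Time to primary and secondary outcomes will be assessed using univariate Cox proportional hazards models". The section on secondary outcomes and sensitivity analyses applies the same Kaplan-Meier approach to mortality, ED visits, hospitalization and acute inpatient dialysis. The sensitivity analyses it lists are repeated-event models (negative binomial, mixed linear, Andersen-Gill) and a covariate-adjusted Cox model.

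Follow-up stops at dialysis: "Participants will be followed for 1 year or until dialysis initiation" (Figure 1). Table 1 admits only patients whose predicted chance of starting dialysis within two years exceeds 40%. Under Non-Study Treatments, "dialysis modality planning and initiation, kidney transplant referral, and advanced care planning will be left to the discretion of the patients’ clinical care team". The abstract's Background hopes that monitoring will "facilitate more optimal dialysis starts".

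**The concern.** Once a patient starts dialysis or dies, a pre-dialysis ED visit or admission can no longer be observed. Kaplan-Meier treats such a patient as still able to have the event later, at the same rate as those who remain. Its complement therefore describes a population in which nobody starts dialysis or dies. It does not give the share of enrolled patients who actually had an ED visit or admission, which is how clinicians will read the curves.

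A second, smaller issue is dependence. The Introduction attributes ED visits, hospitalization and emergent dialysis to the same causes, including unexpected loss of kidney function and sudden uremic symptoms. The Discussion cites a Manitoba population cohort in which ED use in the week before dialysis was 9 times that of prevalent dialysis patients. Event risk is thus raised close to the moment of censoring. Unblinded teams who see VIEWER data decide when dialysis starts, so the censoring pattern could differ by arm. No listed analysis addresses competing risk or dependent censoring.

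**Working it through.** **Inputs** (Sample Size Considerations and Table 1): usual-care event rate 0.114 per month; "hazard ratio [HR] = 0.61 for intervention", so the VIEWER rate is 0.114 × 0.61 = 0.0695; 12 months of follow-up; censoring 0.03 per month; attrition 10%; two-sided alpha 0.05; 90% power; two-year dialysis risk above 40%.

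**Step 1: reproduce the plan's sample size.** Schoenfeld's formula gives 4 × (1.960 + 1.282)² / (ln 0.61)² ≈ 172, or 173 events with rounding up at each step. With event rate l and censoring rate c, the probability of an observed event by month 12 is l/(l+c) × (1 − exp(−12(l+c))).
- Usual care: 0.114/0.144 × (1 − exp(−1.728)) = 0.651.
- VIEWER: 0.0695/0.0995 × (1 − exp(−1.194)) = 0.487.
- Mean 0.569. Then 173/0.569 gives 305, and 305/0.90 gives 339, or 340 with equal arms.

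The stated 340 reproduces. It already allows for events lost to censoring, so the sample size is not in question.

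**Step 2: 12-month risk by one minus Kaplan-Meier.** This is 1 − exp(−12l) whatever the competing rate: 1 − exp(−1.368) = 74.5% for usual care and 1 − exp(−0.834) = 56.6% for VIEWER, a difference of 17.9 points.

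**Step 3: actual cumulative incidence.** Use the Step 1 formula, with c now the rate of dialysis or death. The document does not say how much of the 3% is dialysis or death, so a range is shown. The entry threshold implies at least −ln(0.60)/24 = 2.13% per month under a constant hazard, which is 22.5% by month 12 if nothing else intervened.

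| Dialysis or death per month (same in both arms) | Usual care | VIEWER | Overstatement by 1−KM (points) | Difference between arms | Overstatement of difference |
|---|---|---|---|---|---|
| 1% | 71.2% | 53.8% | 3.4 and 2.8 | 17.4 | 0.5 |
| 2.13% (entry threshold) | 67.6% | 50.8% | 6.9 and 5.8 | 16.8 | 1.1 |
| 3% (all planned censoring) | 65.1% | 48.7% | 9.4 and 7.9 | 16.4 | 1.5 |
| 4% | 62.4% | 46.4% | 12.2 and 10.2 | 15.9 | 2.0 |

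Reading 11.4% and 3% as monthly probabilities instead of rates changes little: the overstatement in the 3% row becomes 9.6 and 8.1 points.

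**Step 4: the hazard ratio.** This was simulated with 1,000,000 patients per scenario at the plan's rates.
- With dialysis/death independent of the outcome given arm, the cause-specific hazard ratio stayed at 0.61 within simulation error, while VIEWER multiplied the competing rate by anything from 0.5 to 2.0.
- With a shared gamma frailty (variance 0.5 to 1.0) acting on both hazards and no VIEWER effect on ED visits or admissions, the ratio was 1.02 to 1.04 when VIEWER halved the competing rate, 1.00 when it left it unchanged, and 0.96 to 0.94 when it doubled it.

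The frailty variances and rate multipliers are assumptions, not figures from the document.

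**The case against.** The strongest defence is that the plan commits to a between-group log-rank comparison and names no 12-month risk as its estimand. That comparison is valid for the cause-specific hazard, the sample size is sound, and a pre-dialysis endpoint applied equally to both arms is coherent for a study of patients not on dialysis. Mortality and acute inpatient dialysis are also secondary outcomes in their own right. All of this stands, and it limits the point to presentation, labelling and one supportive analysis. It does not remove the point, because Kaplan-Meier is the stated estimator, its curves will be read as risks, and it is carried over to the secondary outcomes.

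A competing-risk analysis could sit in an unseen analysis plan. But the article positively names the estimator and the censoring rule, and it lists its sensitivity analyses. The point rests on that stated choice and not on an omission.

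A reader might infer four stronger things that the document does not support:
- **Any VIEWER effect on dialysis timing biases the hazard ratio.** Step 4 shows that it does not unless dialysis or death shares risk with the outcome.
- **Censoring at dialysis breaches intention-to-treat.** Patients are still analysed as randomized, and ending follow-up at dialysis is part of the design.
- **The cost model is corrupted.** The Economic Assessment says "We will use event rates and direct costs derived from the trial". It does not mention Kaplan-Meier risks, and a Markov model can use rates directly.
- **Fine-Gray regression would cure the bias.** In the null simulations with dialysis or death doubled under VIEWER, the subdistribution ratio was about 0.85, against 0.94 to 1.00 for the cause-specific ratio. It is more sensitive to dialysis timing, not less.

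**Conclusion.** The concern holds for absolute risk. Following the plan as written would overstate the 12-month proportion with an ED visit or admission by about 9 points (usual care) and 8 points (VIEWER) if all of the 3% monthly censoring is dialysis or death, and by about 7 and 6 points at the entry-threshold rate. The between-arm difference would be overstated by about 1.5 and 1.1 points respectively. These figures assume constant hazards and the same competing rate in both arms.

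For the treatment comparison the effect is conditional and modest. The log-rank test and Cox ratio answer a cause-specific question correctly. They depart from 1.00 under no effect by roughly 2% to 6% only if dialysis or death shares unmeasured risk with the outcome and VIEWER halves or doubles its rate. The document makes shared risk plausible but gives no figure for either quantity, and more optimal dialysis starts need not be earlier ones. This should be fixed, but it does not threaten the primary test or the sample size.

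**What to change.** 1. Keep the log-rank test and Cox model as primary, and state that they address the cause-specific hazard of a pre-dialysis ED visit or admission.
2. Replace Kaplan-Meier curves and any 12-month risks with Aalen-Johansen cumulative incidence, treating dialysis and death as competing events. Do this for the primary outcome and for the ED-visit and hospitalization components. For acute inpatient dialysis, treat death and dialysis started in any other way as competing.
3. Report the cumulative incidence of dialysis and of death by arm beside the primary result, so that readers can see whether the censoring differs.
4. Prespecify one sensitivity analysis for dependent censoring. Options are inverse-probability-of-censoring weights using baseline eGFR and KFRE, or a composite that counts death. The weights remove only the dependence that those covariates explain, and the composite deals with death but not dialysis; the plan should say so.
5. If Fine-Gray is shown, present it as descriptive.

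The cost is a few sentences and standard software. Baseline eGFR and KFRE are already collected, mortality is already an outcome, and dialysis start already ends follow-up. The sample size, primary test and visit schedule do not change. The wording should be settled before anyone sees dialysis rates by arm.

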### Secondary Outcomes and Sensitivity Analyses

The same Kaplan-Meier survival curve approach will be used for the secondary outcomes of all-cause mortality, ED visits, hospitalization, and acute inpatient dialysis initiation. Change in overall KDQOL, UK Kidney PREM, and SUS scores will be assessed with a 2-sided t-test or Wilcoxon Rank Sum test as distributionally appropriate and interpreted relative to their minimal important differences. Sensitivity analyses will include (1) negative binomial regression and mixed linear models to account for repeated events; (2) multivariate Cox regression to adjust for any potential imbalances in prognostic covariates; and (3) an Andersen-Gill model to adjust for repeated events in the context of a time-to-event analysis.^
11
^ All outcomes will be assessed at a 2-sided alpha = 0.05. Subgroup analyses will be prespecified and limited to (1) eGFR greater or less than 10 mL/min, (2) sex and gender (described below), and (3) diabetes. A per-protocol analysis will be performed specifically and only to estimate the potential impact of patient non-adherence.

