### Sex and Gender Differences

We will collect information on both sex and gender at enrollment. We will perform a prespecified subgroup analysis given known differences in CKD progression by sex. We will also examine intervention uptake and adherence by gender in a sensitivity analysis, and the primary and secondary outcomes will be adjusted for gender if there are baseline imbalances between arms.

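### KDQOL-SF and PREM are collected at five time points but compared by an unadjusted two-sample test on change; a baseline-adjusted repeated-measures model would be more precise on the same data

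*Protocol article*

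**What the plan says.** Follow-up Visits in the protocol article says that the UK Kidney PREM and the KDQOL-SF "will be measured at baseline, 3, 6, 9, and 12 months (or at baseline and subsequently every 3 months until the initiation of the dialysis". That is one baseline and up to four later assessments, ending early for patients who start dialysis.

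Secondary Outcomes and Sensitivity Analyses gives the method: "Change in overall KDQOL, UK Kidney PREM, and SUS scores will be assessed with a 2-sided t-test or Wilcoxon Rank Sum test", with the choice between the two tests depending on the distribution. For these scores it names no visit, no baseline covariate and no repeated-measures model.

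Linear mixed models appear once, in the list of sensitivity analyses: "negative binomial regression and mixed linear models to account for repeated events". The same list includes an Andersen-Gill model for repeated events.

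Covariate adjustment is mentioned in two places. One is a sensitivity analysis, "multivariate Cox regression to adjust for any potential imbalances in prognostic covariates". The other, under Sex and Gender Differences, says that "the primary and secondary outcomes will be adjusted for gender if there are baseline imbalances between arms". Neither adjusts a questionnaire score for its own baseline value.

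**The concern.** A two-sample test takes one number per patient, while the design collects a series of up to four post-baseline scores. Three consequences follow.

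- **Visits.** The change could be taken at month 12, at the last available visit, or at each visit in turn. The first two use one post-baseline score per patient. The third gives four tests per score, each at 0.05, with no joint model.
- **Precision.** Subtracting the baseline is generally less efficient than regressing on it.
- **Stopping at dialysis.** Questionnaires end at dialysis. A month-12 test would leave out patients who started dialysis earlier, and a last-visit test would mix changes over 3 to 12 months. Dialysis start comes after randomization, and VIEWER might influence it.

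The one mention of linear mixed models is attached to repeated events. Repeat ED visits and admissions are skewed counts over unequal follow-up, which a linear model does not fit well. The repeated scores, which suit such a model, have none assigned to them.

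At stake are the precision and interpretation of two patient-reported secondary outcomes.

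**Working it through.** **The plan's own figure.** The article gives no power or sample size for KDQOL-SF or PREM. Its only such figure is N = 340 for the primary outcome, and it reproduces. With "hazard ratio [HR] = 0.61 for intervention", two-sided alpha 0.05 and 90% power, Schoenfeld's formula gives 173 events. Monthly hazards of 0.114 (events, usual care) and 0.03 (censoring) over 12 months give event probabilities of 0.651 and 0.487, mean 0.569. Then 173/0.569 gives 305 after rounding up, and 305/0.90 gives 339, against 340 stated. Nothing below depends on this figure.

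**Use of the schedule.** There are 5 scheduled assessments. A single change score uses 2 and leaves 3 unused, all of them post-baseline.

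**Precision at one visit.** Let s be the SD of the score at both visits (equal variances assumed) and r the correlation between baseline and follow-up (assumed, since the article gives none). Per patient:

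- variance of change = 2(1−r)s²
- baseline-adjusted variance = (1−r²)s²
- ratio = (1−r²)/[2(1−r)] = (1+r)/2

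| r | Change (s²) | Adjusted (s²) | Ratio |
|---|---|---|---|
| 0.3 | 1.40 | 0.91 | 0.65 |
| 0.5 | 1.00 | 0.75 | 0.75 |
| 0.7 | 0.60 | 0.51 | 0.85 |
| 0.8 | 0.40 | 0.36 | 0.90 |

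The reduction in variance is therefore 10% to 35% over this range. The ratio is for the t-test; the Wilcoxon test is not covered by the formula.

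**In terms of power.** For an assumed true difference of 0.3 SD, change score against baseline-adjusted:

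| Patients per arm | r = 0.3 | r = 0.5 | r = 0.7 |
|---|---|---|---|
| 170 (all randomized) | 65% vs 83% | 79% vs 89% | 95% vs 97% |
| 106 (derived below) | 46% vs 63% | 59% vs 71% | 81% vs 86% |

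**Using all four post-baseline visits.** With complete data and the same correlation r between all visits, the baseline-adjusted mean of four visits has variance [(1+3r)/4 − r²]s². At r = 0.5 this is 0.375s², against 1.00s² for a single change score. At r = 0.3 and 0.7 the ratios are 0.275 and 0.475. This contrast averages over visits, so it answers a different question from a month-12 difference. It shows the information available, not a like-for-like gain.

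**Missing month-12 scores.** Sample Size Considerations gives 3% censoring per month. If that is taken as loss of questionnaires (an assumption), the share still contributing is 0.97^3 = 0.91, 0.97^6 = 0.83, 0.97^9 = 0.76 and 0.97^12 = 0.69. About 30% would have no month-12 score. Adding the 10% attrition, 0.90 × 0.694 = 0.62 remain, so about 38% are missing and 170 × 0.62 is about 106 per arm remain.

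A rough comparison comes from eligibility. A two-year dialysis risk of 40%, the lower limit for entry, implies 1 − √0.6, or about 23%, starting dialysis within 12 months under a constant hazard (also assumed).

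**The case against.** The strongest reply has four parts.

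- **No visit is named.** A reader might infer that the plan throws away three of the four follow-up visits. The text does not say so. The choice of visit and the handling of missing scores may be settled in the full protocol or an SAP that is not shown. This stands, so the unused visits are a consequence of one reading. What remains is that the stated test, on any reading, does not model the visits jointly.
- **A change score already uses the baseline.** A reader might infer that baseline is ignored or that the comparison is biased. Neither follows: with complete data the test is valid under randomization. The loss is in precision and in sensitivity to chance baseline imbalance, on outcomes for which the article claims no power.
- **The inputs are assumed.** The 3% per month is a sample-size input for the primary outcome. The article does not call it questionnaire loss or a dialysis rate, so the 30% is not the plan's own figure. The values of r are likewise not in the document.
- **The mixed-model phrase may be loose wording.** A reader might infer that linear models were deliberately chosen for event counts and should be struck out. The article speaks of repeated events, not counts, and already has negative binomial and Andersen-Gill models for them. The phrase may have been meant for the repeated scores. Deleting it could then remove the analysis that is wanted, so it should be reassigned.

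It is also fair to say that a mixed model does not fully solve the stopping at dialysis. It is valid only under missing at random, and a month-12 contrast can imply scores beyond dialysis or death unless the target is defined.

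**Conclusion.** The point holds as a matter of efficiency and clarity. The article states a method for KDQOL-SF and PREM that is valid with complete data but fits its own measurement schedule poorly. This is a stated choice, not a detail left open.

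Baseline adjustment alone would bring the variance to 0.65 to 0.90 of the change-score variance, given equal variances and r between 0.3 and 0.8. A joint model would also use the earlier scores of patients with no month-12 value: about 30% if the 3% monthly censoring is read as questionnaire loss, about 38% with the 10% attrition added. The sentence on linear mixed models needs correcting whichever meaning was intended.

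Only secondary and sensitivity analyses are affected. The primary log-rank comparison and the sample size of 340 stand.

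**What to change.** 1. Analyse KDQOL-SF and PREM with a mixed model for repeated measures on all post-baseline scores. Include baseline score, site, visit, arm and arm-by-visit, and name the primary contrast in advance (for example the month-12 difference or the average over visits).
2. State that the model relies on missing at random and that the target is the score before dialysis. Add a sensitivity analysis for scores that stop at dialysis or death.
3. Reword the list of sensitivity analyses so that linear mixed models apply to the repeated scores. Negative binomial regression (with log follow-up time as offset) and the Andersen-Gill model then apply to repeated events.

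While that sentence is open, the SUS entry also needs attention, as a separate matter. Under Follow-up Visits, usability "will be assessed at the end of the trial (12 months or at the time of dialysis initiation) using the System Usability Scale (SUS) survey", so there is no baseline from which to take a change.

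The cost is wording and some programming before analysis. No extra data, visits or patients are needed.

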**Measurements::**

Participants randomized to the intervention group will be provided with the VIEWER platform, comprised of a wireless blood pressure (BP) monitor, weight scale, transcutaneous O_2_ sat (SpO2) monitor, wearable motion tracker, and mobile tablet running the VIEWER application. The intervention group will be trained to use the VIEWER platform to complete a daily self-assessment via the app (BP, weight, O_2_ saturation, step count) and weekly Edmonton Symptom Assessment System Revised (ESAS-r) survey. These assessments will be integrated into clinical decision-making in multidisciplinary kidney health clinics. Participants will use the VIEWER platform for 12 months (or until dialysis initiation) in addition to receiving usual care.

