### Control Group

Patients randomized to the control group will see their multidisciplinary CKD care teams as per usual care, either virtually or in-person.

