^ Both advanced CKD and HF share a significant number of similarities and exhibit symptoms which can be identified early and managed remotely, making virtual monitoring a promising preventative tool.^
6
^ As such, virtual monitoring in advanced CKD patients has the potential to improve health outcomes with a monitoring program that is specifically tailored to CKD.

The VIEWER is a disease-specific intervention which is looking at monitoring parameters relevant to the care of CKD patients who are approaching kidney failure and need to start dialysis. The VIEWER was created by a team of nephrology clinicians, data scientists, patient partners, and information technology collaborators. Significant effort went into making this platform accessible and easy to use.

The VIEWER provides daily data on BP, weight, blood oxygen saturation levels (SpO_2_), and physical activity levels. We pilot tested VIEWER in 36 CKD patients (80% with diabetes, average age 74, 46% female) to assess usability, acceptability, and adherence, and gather patient feedback.^
20
^ Results showed high usability (90/100 on SUS scale) and acceptable adherence with daily self-assessments (78%) (18).^
20
^ Even though adherence decreased at 3 months, >80% of participants continued to use the kit at least twice weekly even at 3 months.^
20
^ In total, 70% of participants asked if they could keep using the kits after the study, suggesting high acceptability.^
20
^

The VIEWER, a tablet-based virtual care platform for CKD patients, has the potential to manage CKD and reduce the likelihood of adverse outcomes such as ED visits and hospitalization. The proposed trial will rigorously test whether this platform deployed in realistic clinical settings can improve important patient outcomes.

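### A conventional per-protocol analysis can exclude patients from the VIEWER arm only, so it would be a biased measure of the impact of non-adherence if adherence tracks prognosis (minor; the ITT result is unaffected)

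*Protocol article*

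**What the plan says.** Under Secondary Outcomes and Sensitivity Analyses, the protocol article gives one sentence on the matter: "A per-protocol analysis will be performed specifically and only to estimate the potential impact of patient non-adherence". It names a method and a single purpose. It does not define the analysis set, an adherence threshold, the comparator or an estimator.

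Three other places bear on it:

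- **Who can be non-adherent.** In the abstract (Measurements), "The intervention group will be trained to use the VIEWER platform to complete a daily self-assessment via the app", and a weekly symptom survey is added. Under Control Group, "Patients randomized to the control group will see their multidisciplinary CKD care teams as per usual care". The abstract's Methods paragraph also says that controls are not exposed to the platform.
- **How common non-adherence may be.** The Discussion reports 78% adherence with daily self-assessments in a 36-patient pilot. It continues "Even though adherence decreased at 3 months", and adds that more than 80% still used the kit at least twice a week at that time.
- **The primary analysis.** "Our primary analysis will take an intention-to-treat (ITT) approach", and the outcome "will be compared between groups using a Kaplan-Meier analysis with a log-rank test".

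**The concern.** In a trial where both arms take something, a per-protocol rule can at least be applied to both. Here it cannot, because usual-care patients have no platform use to measure. A rule based on patient non-adherence therefore removes people from one arm and leaves the other whole.

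The patients removed are unlikely to be a random sample. The Introduction links emergency visits to frailty, multimorbidity and sudden deterioration. The Limitations section expects limited health and digital literacy to reduce engagement. If frailer or deteriorating patients measure themselves less, the VIEWER patients who remain are at lower risk than the full control arm for reasons unrelated to VIEWER.

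What is at stake is the one purpose given for the analysis. The gap between the per-protocol and ITT estimates would mix the effect of using the platform with the better prognosis of those who use it. A per-protocol hazard ratio below the ITT value could then be mistaken for evidence that VIEWER works when used.

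**Working it through.** **1. The plan's own figure.** Inputs from Sample Size Considerations: HR 0.61, control event rate 11.4% per month, censoring 3% per month, 12 months, 10% attrition, two-sided alpha 0.05, 90% power.

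- Events (Schoenfeld): 4 × (1.960 + 1.282)² / (ln 0.61)², which rounds up to 173.
- Event probability, λ/(λ+c) × (1 − exp(−12(λ+c))): 0.651 for control (λ = 0.114, c = 0.03) and 0.487 for VIEWER (λ = 0.61 × 0.114). The mean is 0.569.
- N = 173 / 0.569 ≈ 304.0, rounded up to 305. Then 305 / 0.90 = 339, against the stated 340.

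The sample size reproduces, so no stated figure is wrong. After attrition, 170 × 0.90 = 153 per arm.

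**2. Direction, in closed form.** Suppose VIEWER has no effect. Let p be the share of patients who would adhere and k the hazard of non-adherers relative to adherers. The control arm holds both types and the per-protocol VIEWER set only the first. The hazard ratio at the start of follow-up is therefore

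HR = 1 / (p + (1 − p)k).

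| p | k = 1 | k = 1.5 | k = 2 | k = 3 |
|---|---|---|---|---|
| 0.90 | 1.00 | 0.95 | 0.91 | 0.83 |
| 0.78 | 1.00 | 0.90 | 0.82 | 0.69 |
| 0.60 | 1.00 | 0.83 | 0.71 | 0.56 |

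For example, 1 / (0.78 + 0.22 × 2) = 1 / 1.22 = 0.82. With k = 1 there is no bias. The documents give no value for k, so these are assumed values.

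**3. Size, by simulation with no true effect.** Inputs: 153 per arm, the plan's control event rate, 3% per month independent censoring and 12 months. VIEWER adherers were compared with all controls. The log-odds of adherence fall by 0.5 to 1.0 per SD of log-frailty (assumed). Two frailty distributions were used, both assumed: log-normal with SD 0.5 to 0.8 (4000 runs per scenario) and gamma with variance 0.5 to 1.0 (3000 runs).

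| Share adherent | Frailty | Mean per-protocol HR | Two-sided rejection |
|---|---|---|---|
| 78% | log-normal | 0.95 to 0.89 | 5.9% to 12.0% |
| 78% | gamma | 0.94 to 0.87 | 6% to 13% |
| 60% (assumed) | log-normal | 0.92 to 0.81 | 8.0% to 23.4% |
| 60% (assumed) | gamma, variance 1.0 only | 0.86 to 0.77 | about 12% to 27% |

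In the log-normal runs, rejections in the biased scenarios were almost all in favour of VIEWER. When adherence was unrelated to frailty, the per-protocol HR was 1.00 with about 5% rejection. ITT stayed at 1.00 with 4.4% to 5.4% in every scenario.

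**4. The alternative, with the plan's inputs.** The 12-month risks are 1 − exp(−0.114 × 12) = 74.5% and 1 − exp(−0.61 × 0.114 × 12) = 56.6%, a difference of 17.9 points. Divided by the adherent share, this is 17.9 / 0.78 = 22.9 points, or 17.9 / 0.90 = 19.9 points if a lower threshold classed an assumed 90% as adherent. If the true ITT difference is zero, so is the ratio, whatever the link between adherence and prognosis.

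**The case against.** The strongest objection is that the article never says adherers will be compared with all controls. It gives a label and a purpose. The set definition, and any weighting or adjustment, may be in an analysis plan or full protocol that is not shown, and their absence from an article is not a fault. This stands, and it makes the point conditional. What remains is that the article does fix the method, and that in this design the ordinary meaning of that method excludes patients from one arm only.

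A reader might infer that the planned analysis will look favourable whether or not VIEWER works. The documents do not support that. They do not say that patients who stop measuring are sicker, and without such a link there is no bias.

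Three further objections carry weight:

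- The analysis is explicitly limited in purpose, and nothing in the primary inference or sample size depends on it.
- The pilot's 78% may be the share of assessments completed, not the share of patients who would count as adherent.
- The complier-average effect has its own weak point. It assumes no VIEWER effect in those classed as non-adherent, yet the pilot shows that partial use is common, and partial users would still send readings to their care team. With a strict threshold, the ratio would overstate the effect in adherers.

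**Conclusion.** The point holds as a minor, conditional one. Adherence can be observed in the VIEWER arm only, so a conventional per-protocol contrast loses the randomized comparison and is not a sound estimate of the impact of non-adherence. With no true effect and 78% of patients adherent, the bias is an HR of roughly 0.95 to 0.87 with about 6% to 13% false positives. At the weak end of that range it is barely visible; at lower adherence it grows.

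These sizes rest on three assumptions: that adherence tracks prognosis with the strength simulated, that 78% can be read as a share of patients, and that the set drops non-adherent VIEWER patients while keeping all controls. It would go too far to conclude that the trial is biased or that a false claim of benefit is built in. The ITT analysis keeps its error rate, and the article restricts what the per-protocol analysis is for.

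**What to change.** Replace the per-protocol sentence with a randomization-based estimate: the ITT Kaplan-Meier 12-month risk difference divided by the proportion of VIEWER patients who meet a prespecified use threshold, with a bootstrap interval. If a per-protocol table is kept, label it descriptive.

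Set the threshold low, so that only minimal or no use counts as non-adherent, and fix it before outcomes are compared by arm. State the assumption that VIEWER has no effect in patients below the threshold.

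The cost is one changed sentence and a few lines of code. The interval is wider than the ITT interval on the risk-difference scale by about 1 / 0.78 = 1.28 times at 78% adherent, or 1 / 0.90 = 1.11 times at an assumed 90%, before allowing for uncertainty in the proportion. The primary analysis and the sample size do not change.
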